### Design of the study

This proof-of-concept trial will follow a randomized and blinded staggered-onset design for the initial three months after implantation, followed by open-label active stimulation in all subjects for a total of 24 months after implantation, with systematic monitoring of safety and efficacy. This design has been used in other recent successful early clinical proof-of-concept trials of DBS in psychiatric conditions[148]. The staggered onset of active stimulation permits assessment of the possible effect of electrode insertions without stimulation (‘microlesioning’) of the amygdala target. We expect greater improvement in PTSD symptoms in patients with initial active DBS, compared with sham stimulation, and improvement in the subgroup initially randomized to sham after stimulators are subsequently activated. The comparison of sham to active stimulation also permits a direct comparison of possible adverse effects of BLn DBS to insertion of inactive electrodes. We feel that the 2-month delay in receiving active treatment for those subjects randomized to initial sham stimulation is justified based on the scientific value of the comparisons noted, given the previously untested nature of the intervention. For ethical and investigative reasons, all subjects will receive active stimulation beginning at three months after implantation. In both treatment-refractory OCD[72] and depression[81], the benefits of stimulation increased over a 1- to 2-year period after initiation, leading us to design this pilot study with a 2-year investigational period after implantation. Given the chronic nature of illness in the subjects to be included in this study, it also makes sense heuristically to expect optimal benefit to take up to 2 years to be manifest. Equally important is the potential for adverse effects of long-term amygdala DBS to build or change over time.

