### Outcome measures

The following measures will be used to assess symptomatic and functional outcomes [see Additional file1 for detailed description of measures 1 to 4]:PTSDClinician Administered PTSD Scale (CAPS) [154] Davidson Trauma Scale (DTS) [158]Other psychiatric symptomology/morbidity Montgomery-Asberg Depression Rating Scale (MADRS) [157]Young Mania Rating Scale (YMRS) [159]Columbia-Suicide Severity Rating Scale (C-SSRS) [160]Hamilton Anxiety Rating Scale (HARS) [161]Functioning/quality of lifeGlobal Assessment of Functioning (GAF) [162]Veterans Quality of Life Assessment (SF-36 V) [163]Life Function in PTSD (LFIPS) [see Additional file 2]Global outcomeClinical Global Impression of Severity and Improvement (CGI-S & CGI-I) [164]Neuropsychological measuresAmygdala Deep Brain Stimulation in PTSD Scale (ADIPS) [see Additional file 3]. Given that amygdala DBS has not previously been performed in humans with PTSD, we will also administer a unique neuropsychological battery, the Amygdala DBS in PTSD Scale (ADIPS), which was developed for this study. This battery is designed to systematically assess effects of electrode insertion and stimulation on cognitive, perceptual, emotional, and behavioral functions known to be influenced by the amygdala and its connections.Neuropsychological Battery [see Additional file 4]. This battery consists of standardized measures of attention, concentration, mental effort, verbal and nonverbal memory, language, visuospatial abilities, and executive skills. It will be administered at baseline and at 6, 12, and 24 months postimplantation by a certified neuropsychologist (RM).Functional neuroimaging. Preoperatively, patients will undergo a provocative PET-CT scan using fluorodeoxyglucose F-18 (FDG) to determine the baseline activity of the amygdalae, insulae, cingulate and mPFC regions as in previous studies [109, 110]. The PET procedure will include both a resting baseline study, and a second ‘stimulus provocation study’, during which patients will listen to an audio recording of a ‘trauma script’ made prior to the scanning session. The script will consist of the patient’s recitation of a narrative of the trauma that caused PTSD as in prolonged exposure therapy (for example, [47]). Study Psychiatrists (RK, HS) will be present during the PET session to ‘titrate’ symptom severity to moderate, but not intolerable levels of arousal. The same ^18^FDG PET scan paradigm will be repeated at 15 months postoperatively with optimal DBS programming parameters. Since patients enrolled in this study have failed psychotherapy, including exposure-based therapy, we expect that changes in amygdala activation observed on the second PET scan will not be the result of therapeutic habituation from the first exposure session, but rather the effect of DBS. We will compare ^18^FDG PET metabolism in the target regions between resting and stimulus-exposed conditions, and differences from preoperative to approximately one year after chronic DBS. Our data analysis of the PET scans will follow the described theory of parametric mapping using SPM (Wellcome Trust Centre for Neuroimaging) [165]. With this software, the PET data in each voxel will be normalized and fitted in a linear statistical model. Following the technique described by Shin and others [102], our hypotheses will be evaluated as contrasts where the linear compounds of the model parameters will be evaluated with t-tests. This data is then transformed into a z-score. Since we have strong directional hypotheses (that DBS reduces amygdala hyperactivity in PTSD patients), we will consider z >3.09 (*P* <0.001 one tail, cluster level) as a statistically significant difference. In this study, MM and DS will conduct and analyze the PET scans.Electroencephalographic changes. After the one-month post-implantation EEG telemetry session, patients will have routine EEGs performed monthly for 15 months, and then every three months for the last nine months of the study. These will be analyzed by our study neurologist, JC, with particular attention paid to development of epileptiform changes.

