### Study aims

The primary aim is to assess the safety and identify adverse events of BLn DBS for treatment-resistant PTSD. Safety assessments include the following:Frequency and severity of all adverse events including physiological, neurological and psychological/neuropsychological (see below).Occurrence of adverse events in relation to DBS amplitude, frequency and pulse width.Occurrence of electrophysiological events in relation to DBS amplitude, frequency and pulse width.Electroencephalographic changes over time.

The secondary aim is to assess the effect of BLn DBS in treatment-resistant PTSD on psychiatric symptoms and quality of life using measures detailed below. A reduction of PTSD symptoms, as evidenced by the CAPS score, with a 30% reduction from baseline is defined as a response. For this study, the CAPS for DSM-IV will be used, as the protocol was developed before publication of the DSM-5[166] or the CAPS for DSM-5. The effects of BLn DBS on other psychiatric and neuropsychiatric functions will be assessed during the course of stimulation, and changes in either beneficial or adverse directions recorded and tabulated.

The third study aim will be to assess changes in brain metabolism by comparing the ^18^FDG PET scan obtained before implantation to that obtained 15 months post-implantation. Regions of interest will be the bilateral amygdalae, insulae, anterior cingulate gyri (and subregions), and other portions of vmPFC.

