The study includes two specific elements that hope to add to the understanding of brain-behavior relationships from our intervention. First, the double-blind staggered-onset sham-stimulation phase will allow us to observe changes associated with electrode implantation without electrical neuromodulation; what others have referred to as a ‘microlesioning effect’. This will also allow us to separate out nonspecific aspects of study involvement from specific effects of DBS. The study also includes prestimulation and poststimulation PET scanning sessions, each of which includes scans done before and after exposure to a trauma narrative as has been done in other functional neuroimaging studies of PTSD. We chose to use the ^18^FDG PET paradigm because it permits assessments of change in stimulus-driven functioning of the brain for longer time epochs than either ^15^O_2_ PET or fMRI. We feel that this more closely models the clinical difficulty patients with PTSD face; it is not just the nature and intensity of reactions, but their duration and ensuing effect on functioning that is important. We considered including a pre-implantation, as well as a pre-stimulation, post-implantation PET study. While this would be ideal from a scientific perspective, we decided that the additional patient burden was not justified given the completely uncharted territory of this pilot investigation.

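### The planned PET comparison cannot separate stimulation from lead insertion or elapsed time, yet the protocol expects any amygdala change to be the effect of DBS

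*Protocol article*

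**What the plan says.** Outcome measures (functional neuroimaging) places the first session before surgery: "Preoperatively, patients will undergo a provocative PET-CT scan using fluorodeoxyglucose F-18 (FDG) to determine the baseline activity of the amygdalae". The second comes after more than a year of treatment: the "PET scan paradigm will be repeated at 15 months postoperatively with optimal DBS programming parameters". Each session has a resting scan and a scan during a recorded trauma script, so four scans per patient are planned. The comparisons listed are rest against script, and "differences from preoperative to approximately one year after chronic DBS". They are to be evaluated as contrasts in a linear model, with z > 3.09 (one-tailed P < 0.001, cluster level) as the criterion, because the authors hold a directional hypothesis that DBS reduces amygdala hyperactivity.

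Study aims makes this the third aim, comparing the "PET scan obtained before implantation to that obtained 15 months post-implantation".

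On interpretation, Outcome measures reasons that these patients have already failed exposure-based therapy. It therefore expects that a change at the second session will not be habituation "from the first exposure session, but rather the effect of DBS".

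Elsewhere, insertion is kept apart from stimulation. Design of the study says that the staggered onset "permits assessment of the possible effect of electrode insertions without stimulation", and the Discussion repeats the point. The Discussion also reports that a post-implantation, pre-stimulation PET would have been scientifically ideal, but "we decided that the additional patient burden was not justified".

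**The concern.** The hypothesis concerns stimulation, but the contrast spans everything that happens between the two sessions. One rival explanation, habituation, is argued away, and DBS is then the only explanation offered. A second rival, an effect of placing leads in the very structure being measured, is one the protocol takes seriously enough to build a blinded sham phase around. That phase contains no PET scan. Elapsed time is a third: Participants holds psychotropic medication constant for the first six months only (with exceptions for clinical need), well short of month 15.

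At stake is what the trial may conclude. A significant fall in amygdala uptake would be reported as a mechanism of stimulation, when the data would show only that uptake fell after implantation plus stimulation plus 15 months.

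**Working it through.** **1. What differs between the two sessions.**

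| | Before implantation | 15 months after |
|---|---|---|
| Leads in the amygdala | no | yes, all subjects |
| Stimulation | none | on, all subjects |
| Months of stimulation, 30-day onset group | 0 | 15 − 1 = 14 |
| Months of stimulation, 90-day onset group | 0 | 15 − 3 = 12 |

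Onset times come from Randomization and blinding. Design of the study confirms that everyone is stimulated from month 3.

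Write I for the insertion effect still present at 15 months, S for the stimulation effect and T for change over time. The expected pre-post change is I + S + T: one observed quantity, three unknowns. Randomization does not help, because at month 15 the groups differ only by 14 versus 12 months of stimulation. Their difference speaks to two extra months, not to S. The period in which one group is implanted and unstimulated ends at month 3, before any post-implantation PET.

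**2. The stated threshold.** 1 − Φ(3.09) = 0.0010, so z > 3.09 and one-tailed P < 0.001 agree. That figure is correct. It limits chance findings under no change at all (I + S + T = 0). It does not limit findings produced by I or T.

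**3. Can insertion alone cross the threshold?** The documents give no insertion effect on FDG uptake, so this step only illustrates the logic. Assume a paired t-test on one region in 6 subjects (5 df), S = T = 0, and I = δ standard deviations of the within-subject change. The critical t is 5.892, an observed mean change of 5.892/√6 = 2.41 SD. The probability of significance is the upper tail of a noncentral t with noncentrality δ√6:

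| δ (assumed) | t, 5 df | variance treated as known |
|---|---|---|
| 0 | 0.001 | 0.001 |
| 0.5 | 0.011 | 0.031 |
| 1 | 0.056 | 0.26 |
| 2 | 0.381 | 0.96 |

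These are powers against a chosen shift, and they depend heavily on the variance model. They show that insertion can contribute to significance. They do not estimate how often it would.

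In a simulation under the same assumptions, with a post-implantation, stimulators-off scan as the reference and insertion shifts of 1, 2 and 3 SD that persist unchanged, the rate stayed at about 0.001. The choice of reference scan is therefore the source of the ambiguity.

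**4. What the planned scans could still offer.** The session-by-condition interaction is (script − rest at 15 months) − (script − rest at baseline). With subscripts for condition, its insertion component is I_script − I_rest. This is zero only if insertion shifts uptake equally in both conditions. An insertion effect on reactivity to the script remains.

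**The case against.** The strongest reply is that the limitation is known and disclosed: the Discussion names the missing scan and gives a reason suited to a first-in-human pilot. The sentence at issue states an expectation and addresses one specific rival, habituation. The third aim is worded neutrally, as a change in metabolism, and Data analysis says that no formal treatment hypothesis will be tested. The article's own evidence also suggests a small insertion effect. Prior findings with amygdala neurosurgery in humans describes DBS as causing minimal tissue disruption, and reports one patient with leads in this target who gained nothing from insertion before the stimulator was activated.

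Most of this stands and limits the point. The missing scan is neither an oversight nor the finding. The single-patient evidence argues against a large insertion effect, although it concerns clinical benefit, not FDG uptake. What does not follow is that the attribution may stay as it is. The Discussion gives the reason for omitting the scan but does not say which inference is lost. Nor can DBS be read as covering implantation, because the Discussion contrasts changes from implantation without neuromodulation with the specific effects of DBS.

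A reader might infer more: that the PET test has a false-positive rate many times its nominal level, that local signal loss at the leads will produce the result, or that a simple pre-post contrast is fixed as the only test. The documents support none of these. They give no size, direction or persistence for an insertion effect on uptake. The listed comparisons are also compatible with an interaction contrast, and the exact choice may properly sit in a fuller document.

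**Conclusion.** The point holds as one of attribution. The planned PET comparison estimates the combined effect of implantation, stimulation and elapsed time, and the article's expectation that a change is the effect of DBS goes beyond that. This follows from the scan schedule alone and needs no assumption about magnitude. The size of the possible error cannot be stated: with no residual insertion or time effect the attribution would be right, and with a substantial one it would be wrong. The table above rests on assumed shifts and a simplified single-region test, so it supports only the statement that insertion can contribute to significance. The z threshold itself is correct. The consequence is confined to the third aim. The safety aim and the sham-controlled symptom comparison are untouched.

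**What to change.** 1. In Outcome measures, replace the closing attribution to DBS with a statement that a change at the second session would reflect the combined effect of implantation and stimulation, together with elapsed time.
2. Word the directional hypothesis and the reported PET conclusion in the same terms.
3. Refer at that place to the Discussion paragraph on the omitted post-implantation, pre-stimulation scan, and say there that its absence prevents separating insertion from stimulation on PET.

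These are wording changes only, with no extra scan, visit or patient burden.

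Optionally, report the session-by-condition interaction from the four planned scans as a sensitivity analysis alongside the simple pre-post contrasts. The report should say that it removes only an insertion effect equal at rest and under provocation. The same section describes two patients whose responses to stressful cues fell after amygdala lesions (far larger than a lead track), so an effect on reactivity cannot be excluded. The simple contrasts should keep their place, because Rationale for targeting the amygdala also cites raised resting amygdala activity in combat veterans with PTSD. The cost is one additional contrast, with a somewhat larger variance than a simple pre-post difference.

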### Data analysis

This pilot study involves a small number of patients and no formal treatment hypothesis will be tested. Demographics of the patients along with baseline data and clinical information will be recorded and reported. Assessment of psychological scales and neuropsychiatric tests will be conducted according to the recommended methodology. We will compare the patients’ psychological scale scores with their baseline scores mainly for safety reasons and to ensure that our subjects are not worsening. To that end, the primary outcome measure will be the CAPS at 12 months follow-up compared to baseline. We will also analyze responders versus nonresponders to determine if any predictors can be identified. For this purpose, a clinical response will be defined as a 30% reduction in CAPS[154] from baseline and a CGI-I[164] score of 1 (very much improved) or 2 (much improved).

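### The PET significance rule labels an uncorrected single-voxel threshold (z >3.09) as a cluster-level P <0.001, so the stated error rate does not apply to the rule as written

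*Protocol article*

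**What the plan says.** The rule is in the protocol article, Outcome measures, under functional neuroimaging. The unit of analysis is the voxel: "the PET data in each voxel will be normalized and fitted in a linear statistical model". The statistic is then defined: "the linear compounds of the model parameters will be evaluated with t-tests. This data is then transformed into a z-score". The decision rule follows: "we will consider z >3.09 (*P* <0.001 one tail, cluster level) as a statistically significant difference". The one-tailed choice is justified by a single named hypothesis, that stimulation lowers amygdala hyperactivity. Two comparisons are planned: resting against trauma-script conditions, and before surgery against about one year of stimulation.

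Regions appear in two places. Outcome measures says the preoperative scan is done "to determine the baseline activity of the amygdalae, insulae, cingulate and mPFC regions". Study aims, third aim, says: "Regions of interest will be the bilateral amygdalae, insulae, anterior cingulate gyri (and subregions), and other portions of vmPFC". The Data analysis section says that "no formal treatment hypothesis will be tested".

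**The concern.** The sentence joins three things that do not belong together: a voxel-height cut-off, the tail probability of that cut-off for one statistic, and a label saying the probability holds at cluster level. A reader would take a reported PET change to carry a 0.1% chance of being false over the region searched. That probability belongs to one voxel named in advance.

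The rule carries weight. The follow-up scan is at 15 months, and the Design of the study section has all subjects on active stimulation from three months after implantation, so the before-versus-after PET comparison has no sham arm. Outcome measures also says that a change in amygdala activation will be read as an effect of stimulation. The threshold is thus the main guard against a chance finding being reported as a mechanism and carried into later trials.

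**Working it through.** **1. Reproduce the plan's figure.** Input: z = 3.09, one tail (Outcome measures). 1 - Φ(3.09) = 0.0010008, and the one-sided 0.001 point is z = 3.0902. The stated P is exactly the tail area of a single statistic. No cluster extent, smoothness or search volume enters it, so it cannot be a cluster-level P.

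**2. What the cut-off means with six subjects.** If the group test is a paired t with 5 df (an assumption, as the model is not specified), z = 3.09 corresponds to t = 5.89. The mean change divided by its SD must then be at least 5.89/√6 = 2.41.

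**3. Chance of a false finding over a region.** The documents give no volumes and no smoothness. Assumptions: volume per side of 1.5 mL (amygdala), 7 mL (insula), 6 mL (anterior cingulate) and 8 mL (vmPFC), each treated as a sphere, total 2 × 22.5 = 45 mL; smoothness 8 to 16 mm FWHM.

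For a Gaussian field, the expected Euler characteristic at height u is E = Σ R_d ρ_d(u), summed over d = 0 to 3 and over regions, and the chance of at least one exceedance is about 1 - exp(-E). For a sphere of radius r, volume V and smoothness F, R = 1, 4r/F, 2πr²/F², V/F³. At u = 3.09, ρ = 0.00100, 0.00224, 0.00459, 0.00844.

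Example, one amygdala with F = 8 mm: r = (3 × 1500/4π)^(1/3) = 7.10 mm, so R = 1, 3.55, 4.95, 2.93. The sum is 0.0010 + 0.0079 + 0.0227 + 0.0247 = 0.0564. Two sides give E = 0.113, and 1 - exp(-0.113) = 0.107.

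As a check with the small sample, null maps for six subjects were simulated (one-sample t, 5 df, cut-off 5.89, 4 mm voxels, 1500 runs per setting).

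| Search region, one contrast | Gaussian field, FWHM 8 / 12 / 16 mm | Simulated t (5 df), FWHM 8 / 12 / 16 mm |
|---|---|---|
| Bilateral amygdalae | 10.7% / 4.6% / 2.7% | 5.1% / 3.3% / 3.3% |
| All four regions, both sides | 72% / 38% / 22.5% | 45% / 36% / 27% |

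A second simulation on a 3 mm grid, with slightly different assumed volumes (3.4 and 47 cm³) and FWHM 8 to 12 mm, gave 6-9% and 49-68%, inside the same ranges.

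**4. The mildest reading.** If one mean value were tested in each of eight regions (four on each side, taken as independent), the chance is 1 - (1 - 0.0010008)^8 = 0.008.

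**5. Against the stated 0.1%.** The ratio is about 8 for eight regional means, about 27 to 107 for a voxelwise search of the amygdalae, and about 225 to 720 for a voxelwise search of all listed regions.

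**The case against.** The best defence is that this is one paragraph of a journal article that names its software and cites a published technique. An extent threshold or small-volume correction may stand in a fuller document, and the cluster-level label may be shorthand for one. A reader might infer from the silence that no correction will be made. The article does not support that, and missing detail alone would not be a finding. The defence does not save the sentence, though. If 3.09 only forms clusters, exceeding it is not yet a significant result. If 0.001 is a corrected cluster P, then z >3.09 is not the criterion, and its exact match to the single-voxel tail is unexplained. As a per-voxel rate, 0.001 is correct; it is the level attached to it that is wrong.

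Four stronger readings do not hold.

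- A reader might quote one factor by which the error rate is wrong. The size depends on volumes and smoothness that are not given, and on the label not implying a further cluster rule.
- A reader might add a third contrast, the interaction of the two comparisons, and multiply the risk. The article names two, and resting against provoked is not by itself an effect of stimulation.
- A reader might see the two region lists as contradictory. They are better read as nested: anterior cingulate lies within cingulate and vmPFC within mPFC, and the broader list describes the baseline scan.
- A reader might see a direct conflict with the Data analysis statement that no formal treatment hypothesis is tested. That section goes on to discuss psychological scales, CAPS and clinical response, so the tension with a PET threshold is real but mild.

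On weight, the objection is right that PET is the third aim of a six-subject pilot. The primary outcome does not rest on it, and the authors intend to publish complete individual results.

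**Conclusion.** The point stands as a mislabelled error rate. The rule as written attaches a cluster-level P <0.001 to what is arithmetically an uncorrected single-voxel threshold, so the stated 0.1% is not the false-positive rate of the decision. The mislabelling needs no assumption. Its size does: with the volumes and smoothness listed above, and any supra-threshold voxel counted as a finding, the rate in one contrast is about 3-11% for the bilateral amygdalae, the only structure named in the directional hypothesis, and about 23-72% for all listed regions. It would be about 0.8% for eight regional means, but the article specifies a voxelwise fit. This should be fixed before the PET data are analysed; it does not threaten the trial's primary aim.

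**What to change.** In Outcome measures, describe z >3.09 as an uncorrected voxel-height (cluster-forming) threshold and delete the cluster-level P. Call a PET result significant only at family-wise-error-corrected P <0.05, small-volume corrected, for the before-versus-after stimulation contrast in the bilateral amygdalae. Use the region list in Study aims throughout, and report all other regions and contrasts as uncorrected and descriptive.

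An equally acceptable alternative is to label every PET result uncorrected and descriptive, in line with the Data analysis section.

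Either version costs a few sentences, and the correction is a standard option in the named software. The downside is that fewer regions will be called significant. With six subjects that is a real loss, since z >3.09 alone already requires a mean change of about 2.4 SDs if the test has 5 df.

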In humans, the functional neuroimaging review by Etkin and Wager[109] showed significant hypoactivation of the vmPFC in PTSD studies, but not in other conditions (for example, social anxiety disorder and specific phobia) that also have cue-related fear arousal in association with amygdala hyperactivation. Resting state fMRI studies of combat veterans with PTSD completed since we initially developed this protocol have confirmed and extended this pattern. In a study of OEF/OIF combat veterans using the amygdala as a seed, Sripada and colleagues[123] demonstrated increased amygdala connectivity with the insula and hypothalamus, and reduced functional connectivity with the dorsal and rostral anterior cingulate cortex, in those with, compared to those without, PTSD. Rabinak *et al*.[124] also showed increased amygdala-insula connectivity. Hayes and colleagues[125] found a direct correlation between amygdala hyperactivity and vmPFC hypoactivation in a quantitative meta-analysis of 26 fMRI and PET symptom-provocation studies in adult PTSD, even though their meta-analysis demonstrated amygdala hyperactivity in studies with cognitive-emotional, but not symptom -provocation tasks. Most recently, Brown *et al*.[126] found that combat-exposed veterans with, compared to those without, PTSD had reduced functional connectivity between the BLn specifically, and prefrontal regions mediating cognitive control of emotional responses.

Taken together, the findings reviewed suggest the possibility that patients whose PTSD symptoms do not respond to exposure therapy or other interventions may have unremitting amygdala hyperarousal that is resistant to, or insufficiently suppressed by, cognitive efforts normally mediated by vmPFC activation.

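### The PET significance rule is labelled cluster level, but its P <0.001 is the uncorrected single-point tail of z = 3.09, and no cluster-extent or search-volume correction is stated

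*Protocol article*

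**What the plan says.** The Outcome measures section (functional neuroimaging) says that "the PET data in each voxel will be normalized and fitted in a linear statistical model" and that "our hypotheses will be evaluated as contrasts where the linear compounds of the model parameters will be evaluated with t-tests". The result is converted to a z-score. The decision rule follows: "we will consider z >3.09", glossed as P <0.001, "one tail, cluster level) as a statistically significant difference". The reason given for one tail is "strong directional hypotheses (that DBS reduces amygdala hyperactivity in PTSD patients". The comparisons are resting against trauma-script conditions, and before implantation against about one year of stimulation.

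The Study aims section makes PET the third aim and sets its scope: "Regions of interest will be the bilateral amygdalae, insulae, anterior cingulate gyri (and subregions), and other portions of vmPFC".

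The Data analysis section states: "This pilot study involves a small number of patients and no formal treatment hypothesis will be tested".

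The article gives no cluster-extent threshold, corrected error level or search volume for the PET maps.

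**The concern.** A z height and a cluster-level P are different things. The first says how extreme one voxel is. The second says how surprising a cluster of a given size is, given the smoothness of the image and the volume searched, and it cannot be read off a z value. An analyst given this rule does not know whether a single voxel above 3.09 suffices or whether a cluster must pass a further test.

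If the z height alone decides, the 0.1% error rate applies to one voxel and not to a search over several regions and contrasts. Outcome measures also says in advance that amygdala change on the second scan is expected to reflect stimulation and not habituation, so a chance finding could be reported as an effect of stimulation.

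Two smaller points belong with this. The one tail is argued for the amygdala only, while the regions of interest are wider, and the Background reports that an imaging review "showed significant hypoactivation of the vmPFC in PTSD studies", so the expected direction need not be the same everywhere. A significance rule for a stimulation effect also sits awkwardly beside the Data analysis statement.

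**Working it through.** **Inputs.** From Outcome measures: z >3.09, P <0.001, one tail, cluster-level label, a model in each voxel, and two sets of comparisons (rest/provoked and pre/post). From Study aims: the regions. Not given anywhere: the number of voxels or resels searched, or the smoothness. These are assumed below.

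**1. Reproduce the stated P.** The upper normal tail is 1 − Φ(3.09) = 0.00100. Conversely, the one-sided z for 0.001 is 3.0902. The stated pair matches as a pointwise, uncorrected tail. The two-sided tail is 0.0020. No cluster size or smoothness enters.

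**2. Search-wide error, independent tests.** For m independent tests, P(at least one false positive) = 1 − (1 − 0.001)^m.

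| m (assumed) | Result |
|---|---|
| 8 (one summary per side for four regions) | 0.8% |
| 50 | 4.9% |
| 100 | 9.5% |
| 500 | 39% |
| 1,000 | 63% |

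Because 0.05/50 = 0.001, the 3.09 cut-off holds a 5% one-sided family-wise rate up to about 50 independent tests. The figures are per contrast. Two independent contrasts of 50 tests each would give the m = 100 row, 9.5%.

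**3. Search-wide error, smooth images.** Neighbouring voxels are correlated, so random-field theory is the closer model. Its leading three-dimensional term for R resels at height u is

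E = R × (4 ln 2)^1.5 / (2π)² × (u² − 1) × exp(−u²/2).

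At u = 3.09 this is E = 0.00844 × R, and P(at least one) ≈ 1 − exp(−E).

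| R (assumed) | E | Result |
|---|---|---|
| 1 | 0.0084 | 0.8% |
| 3 | 0.025 | 2.5% |
| 5 | 0.042 | 4.1% |
| 10 | 0.084 | 8.1% |
| 50 | 0.42 | 34% |
| 100 | 0.84 | 57% |

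The two tables are not interchangeable: 50 resels are not 50 independent tests.

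**4. Reading the tables.** In every row with more than one test, and in every resel row, the result exceeds 0.1%. For a search as small as the amygdalae alone, taken here as a few resels, the error stays modest. It becomes large if the rule runs voxel by voxel over all the listed regions and subregions.

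**The case against.** The strongest defence is that the text itself says cluster level. The article condenses a fuller protocol and defers to statistical parametric mapping and to a cited study's technique. Extent and search-volume settings are commonly left to an analysis plan. If a corrected cluster-level P was meant, the z value is the slip and the error may be controlled elsewhere. This stands as a limit on what can be claimed: uncontrolled error is not established, only that the rule as printed is inconsistent and states no control. It does not remove the point, because the article prints a specific decision rule whose parts do not fit together.

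It is also fair that the regions are named in advance, that 0.001 is strict, and that PET is the third aim of a six-subject pilot whose primary aim is safety. Naming regions reduces multiplicity but does not control it, and the significance sentence does not confine itself to those regions.

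Three stronger readings may tempt a reader and should be resisted:

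- **That Data analysis flatly contradicts the PET rule.** It excludes a formal treatment hypothesis, in a paragraph otherwise about clinical scales, the CAPS and responders. This is a tension to reconcile.
- **That a decrease is being tested in the vmPFC against the plan's own model.** The one tail is justified for the amygdala and never expressly extended to the other regions, and a one-tailed contrast can equally be set for an increase. The direction elsewhere is unstated, not wrong.
- **That six subjects put the cut-off out of reach.** This depends on an unspecified model. A paired test on 5 degrees of freedom needs t above 5.89. Pooling 24 scans (6 subjects × 4 conditions) with subject effects would leave 24 − 6 − 3 = 15 degrees of freedom and need t above 3.73. No power figure can be defended from the article.

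**Conclusion.** The concern holds for the labelling and for the absence of any stated correction. P <0.001 is the pointwise tail at z = 3.09 and cannot also be a cluster-level P. Applied voxel-wise over the named regions and contrasts, the rule does not hold its stated 0.1% error rate.

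How far it exceeds that rate cannot be fixed from the document. With an assumed 1 to 10 resels it is about 1% to 8%, and with 50 resels about 34%. With 50 to 500 assumed independent tests it is 5% to 39%. These figures are per contrast and assume that the z height alone decides.

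The importance is moderate. This is the only stated decision rule for the third aim, and it can be put right in wording before analysis, but no trial decision is attached to the PET result.

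**What to change.** - State that z >3.09 is the cluster-forming height only, and declare significance only at family-wise-corrected P <0.05 within the predefined regions, with the masks (search volume) specified.
- Keep the one-tailed test for the amygdala decrease. For the insulae, anterior cingulate and vmPFC, either state the expected direction in advance or test two-sided.
- Report amygdala change as an estimate with a 95% confidence interval and individual patient values.
- In Data analysis, either call the PET tests exploratory or name them as the exception to the statement that no formal treatment hypothesis is tested.

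The same scans serve, so the cost is some wording and analysis time. The downside is that fewer uncorrected voxels will qualify. Replacing the SPM maps with a mean over an amygdala mask as the main read-out would be a reasonable preference but is not needed to correct the error.
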